##### Pupil diameter

2.5.2.3

The average pupil diameter is a reliable marker of the level of autonomic activation and cognitive load. During the performance of demanding tasks, initial pupil dilation is observed, associated with attentional effort and noradrenergic activation, followed by progressive contraction as mental fatigue develops, reflecting a decrease in locus coeruleus activity and the ability to mobilize cognitive resources (75, 76). Under controlled lighting conditions, the pupil diameter is generally between 3.5 and 4.5 mm when alert, and can reach about 5 mm during periods of high cognitive load. As mental fatigue sets in, a progressive reduction to values close to or below 3 mm is observed, reflecting lower phase variability and pupil responsiveness, as well as a reduction in locus coeruleus activity and cortical vigilance (72, 75, 76).

##### Blink rate

2.5.2.4

The blink rate is a psychophysiological marker sensitive to variations in cognitive load, mental fatigue, and dopaminergic activity. During periods of high cognitive demand, the blink rate tends to decrease significantly, reflecting intensified attentional control and voluntary inhibition of the blink reflex in order to avoid visual interruptions during information processing. However, as mental fatigue sets in, a progressive increase in the blink rate is observed, indicative of a compensatory collapse of the oculomotor system and a reduction in cortical vigilance (72, 77–79). On average, the blink rate is between 15 and 25 blinks per minute (≈0.25–0.42 Hz) in a neutral state, decreasing to 5–15 blinks/min (≈0.08–0.25 Hz) during cognitively demanding tasks, and increasing again to values above 25–30 blinks/min (≈0.42–0.50 Hz) in advanced stages of mental fatigue. This biphasic pattern is widely described as an expression of dopaminergic modulation underlying initial attentional effort and subsequent reduction in cortical vigilance (72, 78).

#### Technical and motor performance

2.5.3

Technical and motor performance will be assessed using the LSPT and the Y-SART, using Witty SEM indicators (Microgate, Bolzano, Italy). These instruments allow the effects of mental fatigue on technical execution, reactive agility and decision-making processes in a sporting context to be quantified with high temporal precision and reliability.

Comparisons between groups will examine whether the ST induces greater impairments in performance metrics compared to a cognitively neutral task. The LSPT will provide data on total execution time, technical penalties, and adjusted score, while the Y-SART will produce reaction and execution times in response to visual stimuli. These comparisons will elucidate the degree to which mental fatigue affects motor fluency, visuomotor coordination, and accuracy under pressure.

Intra-subject analyses in the experimental group will allow for the detection of performance deterioration caused by the ST. By comparing pre- and post-intervention scores on both the LSPT and Y-SART, this approach will help determine whether mental fatigue results in statistically significant reductions in motor and technical efficiency.

The associations between performance metrics and indicators of fatigue (e.g., VAS, EEG, and ETS) will also be examined to explore whether higher levels of perceived or physiological fatigue correlate with slower and less accurate performance. These relationships may help identify which dimensions of fatigue are most predictive of declines in physical performance.

##### LSPT

2.5.3.1

In the LSPT, the variables total execution time, technical penalties, and adjusted score will be analysed, indicators that simultaneously integrate motor speed, technical accuracy, and cognitive efficiency under time pressure. This protocol demonstrates high ecological validity and excellent test-retest reliability for assessing technical proficiency and decision-making performance in football (4, 57). Recent evidence shows that mental fatigue leads to an increase in total time and penalty time, indicating that mentally fatigued athletes are more prone to technical errors, such as missing target zones. This decline in performance appears to stem from a shift in attention towards irrelevant stimuli rather than task-relevant stimuli, resulting in poorer technical execution and slower motor fluency (80, 81).

##### Y-SART

2.5.3.2

The Y-SART will use the Witty SEM system to deliver random light stimuli requiring rapid directional responses. Reaction and execution times will be recorded as indicators of visuomotor coordination and decision-making efficiency under cognitive load. Under conditions of mental fatigue, an increase in reaction time is expected in the Y-SART, reflecting slower perceptual-decision processing and reduced cognitive readiness, while execution time may also show moderate increases due to delayed motor initiation. This pattern is consistent with the evidence that reactive agility performance is particularly sensitive to cognitive overload and fatigue effects (82).

In line with Khalaji et al. (14), who reported impairments in decision-making accuracy and execution speed following mental fatigue induction, the present study employs the LSPT and Y-SART to assess the behavioral impact of cognitive overload in football contexts.

Although the protocol is conducted in a controlled laboratory setting, the selected football-specific tests require multidirectional actions and quick responses to external cues, partially reflecting perceptual and decision-making demands present in match play. The controlled environment helps reduce external influences while maintaining key sport-specific elements.

#### Subjective fatigue measures

2.5.4

Individual perceptions of fatigue will be assessed using the FAS and the VAS, both validated instruments for quantifying subjective mental and physical fatigue.

##### FAS

2.5.4.1

The FAS provides an overall measure of perceived fatigue, covering both physical and mental components. This 10-item unidimensional scale has demonstrated strong internal consistency (α = 0.71–0.89) and excellent test-retest reliability in populations including clinical and athletic samples (32, 42, 83). Its Likert format (1 = “never” to 5 = “always”) allows for the assessment of cognitive, motivational, and energy-related aspects of fatigue, providing a reliable index of baseline fatigue levels. This measure will be used in both the experimental and control groups, allowing comparisons of baseline mental fatigue prior to the Intervention.

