Following baseline assessment, all participants will be randomly assigned to either the experimental group or the control group (Phase 4). The experimental group will perform a cognitively demanding task, the ST, for 30 min, designed to induce mental fatigue through sustained attention and inhibitory control demands. Although the ST does not reproduce the full cognitive complexity of real football match situations, it is widely used in experimental research to induce a controlled state of mental fatigue under standardized conditions (4, 8). In the present protocol, it is not intended to simulate football-specific decision-making demands, but rather to induce mental fatigue prior to sport-specific performance assessment. This separation between fatigue induction and performance testing allows clearer interpretation of the neurophysiological and behavioral consequences of mental fatigue. In contrast, the control group will engage in a low-demand relaxation condition, consisting of reading neutral magazines for the same duration (30 min), thereby maintaining minimal cognitive load while controlling for time-on-task effects.

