### Mental fatigue assessment

2.3

The mental fatigue will be assessed using a multidimensional approach, employing different complementary methods. These will include validated subjective instruments such as the FAS and the VAS, which will be administered digitally during Phase 2. The FAS, developed by Michielsen et al. (42) and validated for the Portuguese population by Alves and Nazaré (43), is recognized for its reliability, presenting high internal consistency (α = 0.870). It consists of 10 items on a 5-point Likert scale (1 = never, 5 = always) and assesses the perception of general fatigue. The items question the frequency of physical and mental symptoms of fatigue. This scale will only be applied at the beginning of the session, as it provides a stable measure of the general state of fatigue, suitable for the participants initial characterization. In turn, the VAS will be applied before and after the cognitive task, given its sensitivity to momentary variations in perceived mental fatigue. It is a single-item measure that asks participants to indicate the intensity of fatigue felt at the moment, by marking a point on a continuous line delimited by two extremes (no fatigue—extreme fatigue). For analysis, the marked position is converted into a continuous numerical measure (0–100). The use of this scale in Portugal is supported by national literature, namely in the studies by Afonso et al. (44) and Alves & Nazaré (43). Both will be administered digitally through the Google Forms platform, ensuring standardization and efficiency in data collection.

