### Statistical analysis

2.6

All statistical analyses will be performed using IBM SPSS Statistics version 29.0 (IBM Corporation, Armonk, NY, USA), with a significance level set at 5% (*p* < 0.05). Descriptive statistics (mean, standard deviation, 95% confidence intervals, and range) will be calculated for all outcome variables, including EEG spectral powers, oculomotor parameters, motor performance scores, and subjective fatigue ratings. These data will be stratified by group (experimental and control) and time (pre- and post-intervention) and presented visually using box plots and line graphs to facilitate interpretation (88, 89).

To assess the effect of mental fatigue, paired t-tests will compare pre- and post-intervention results within each group, while independent t-tests will compare the experimental and control groups at each time point (88, 90). For EEG outcomes, repeated-measures ANOVA models will include Time (pre vs. post mental fatigue) and Recording Condition (eyes open, eyes closed, motor imagery) as within-subject factors, and Group (experimental vs. control) as a between-subject factor (88, 90). Assumptions of normality and sphericity will be evaluated prior to analysis, following established recommendations for repeated measures designs (88, 91). When sphericity is violated, the Greenhouse-Geisser correction will be applied. Effect sizes will be reported using eta squared (*η*^2^), interpreted according to Marôco (90) as small (<0.04), moderate (0.04–0.25), or large (≥0.25). Statistical power (π) will also be reported when applicable (92, 93).

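### Section 2.6 compares the randomised arms by separate t-tests before and after the task: the pre test cannot show an effect, and the post test ignores the pre value

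*Protocol article*

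**What the plan says.** All places are in the protocol article.

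- **Allocation (2.2 Sample):** "Following baseline assessment, all participants will be randomly assigned to either the experimental group or the control group".
- **Between-arm analysis (2.6 Statistical analysis):** under the stated aim of assessing the effect of mental fatigue, "independent t-tests will compare the experimental and control groups at each time point". There are two time points, pre and post. The sentence does not say which outcomes it covers.
- **EEG (2.6):** a separate model is given. "For EEG outcomes, repeated-measures ANOVA models will include Time (pre vs. post mental fatigue) and Recording Condition", with Group as the between-subject factor. No Time by Group model is specified in 2.6 for any other outcome.
- **Discussion (section 3):** a repeated-measures ANOVA for time and group is mentioned, without saying which outcomes it covers.
- **Covariates (2.6):** those listed for ANCOVA or subgroup analysis are demographic and contextual. The outcome's own pre value is not among them.
- **FAS (2.5.4.1):** "This measure will be used in both the experimental and control groups, allowing comparisons of baseline mental fatigue prior to the Intervention". The same section says: "The FAS provides an overall measure of perceived fatigue, covering both physical and mental components". Section 2.3 says the scale "assesses the perception of general fatigue", and adds: "This scale will only be applied at the beginning of the session, as it provides a stable measure of the general state of fatigue".
- **VAS (2.3):** "the VAS will be applied before and after the cognitive task, given its sensitivity to momentary variations in perceived mental fatigue".

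**The concern.** Because participants are randomised after the baseline measurements, any difference between arms at the pre time point is due to chance. A significance test there asks a question whose answer is already known, and it cannot bear on the effect of the Stroop task, which has not yet been performed.

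The post-task test does bear on the effect, but it discards the pre value. In a trial of 34, sizeable chance imbalances are common. The pre test neither removes them nor detects them reliably. When one occurs, the post comparison carries part of it, and the precision that the pre value could give is lost.

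The FAS wording is a smaller matter. By the protocol's own description the scale is a total over physical and mental symptoms, so similar totals in the two arms would not show similar mental fatigue.

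**Working it through.** **The plan's own figure.** Section 2.2 gives N = 34 (17 per group) for a repeated-measures ANOVA with two groups and two times, f = 0.25, alpha 0.05 and power 80%. Using the noncentral F for the within-between interaction, with noncentrality f² × N × 2/(1 − ρ) and 1 and N − 2 df, an assumed ρ = 0.5 gives N = 34 with power 0.807. The figure reproduces, and 17 per arm is used below. Two-sided tests are assumed, since sidedness is not stated.

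**1. Smallest baseline difference that reaches p<0.05.** Standard error of a difference in means, in SD units: √(2/17) = 0.343. Critical value t(0.975, 32 df) = 2.037. Threshold: 2.037 × 0.343 = **0.70 SD**.

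**2. How often chance gives a sizeable imbalance (normal approximation).**
- P(|difference| > 0.5 SD) = 2 × [1 − Φ(0.5/0.343)] = **14.5%**.
- P(|difference| > 0.70 SD) is about 4%.
- The remainder, between 0.5 and 0.70 SD, is about **10%**. These imbalances would be reported as non-significant.

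**3. What an imbalance does to the unadjusted post comparison.** Given an observed pre difference d and pre-post correlation r, with no treatment effect, the expected post difference is r × d. The protocol gives no r, so 0.5 to 0.7 is assumed.
- r = 0.5: 0.5 × 0.5 = **0.25 SD**.
- r = 0.7: 0.7 × 0.5 = **0.35 SD**.

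Conditional type I error of the post-only test at d = 0.5, r = 0.5 (normal approximation): the conditional SE is 0.343 × √(1 − 0.25) = 0.297. The upper tail starts at (1.96 × 0.343 − 0.25)/0.297 = 1.42, and with the small lower tail the total is about 8% instead of 5%. Averaged over all randomisations it is 5%.

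**4. Precision given up.** Adjusting for the pre value multiplies the residual variance by about 1 − r²: 0.75 at r = 0.5 and 0.51 at r = 0.7, before the loss of one degree of freedom.

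**5. Chance positives among the pre tests.** The baseline variables that are neither EEG nor gaze number 7: FAS, VAS, 3 LSPT (execution time, penalties, adjusted score) and 2 Y-SART (reaction and execution time).
- If independent: 1 − 0.95⁷ = **30%** for at least one p<0.05.
- At an assumed correlation of 0.5 between variables (simulation, 4,000 runs): about **22%**.
- Leaving out the FAS, for which no test is named: 1 − 0.95⁶ = 26.5% if independent.

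**6. Sensitivity to sample size.** Table 1 gives 24 men and 24 women instead of 34 in total. At 24 per arm the threshold is 0.58 SD, and 8.3% of randomisations exceed 0.5 SD. The problem is smaller but remains.

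**The case against.** The strongest reply is that the pre test is harmless. No stated rule acts on a baseline p-value: it does not gate an analysis, select a covariate or trigger re-randomisation. The phrase about each time point may be a blanket expression. This stands, and it limits the harm of the pre test itself to interpretation.

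A second reply is that the shift in the post comparison is not caused by baseline testing. It comes from the lack of adjustment and would remain if every pre test were deleted. This is also correct, which is why adjustment is the main change and dropping the pre tests is secondary. Randomisation also keeps the post-only test valid unconditionally.

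A third reply is that the Discussion mentions a time-by-group ANOVA, the type of design used for the sample size, so the post-only test may not be the only between-arm analysis. That may be the intention. But section 2.6 specifies such a model for EEG only, so the two sections need reconciling.

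A reader might infer more than the text supports:
- *That the FAS is significance-tested for balance.* Section 2.5.4.1 names a comparison, which a table by arm would satisfy. Section 2.3 gives its purpose as initial characterisation.
- *That every outcome is t-tested at baseline.* The t-test sentence names no outcomes and EEG has its own ANOVA. Gaze recording at baseline is unclear: section 2.4 mentions eye tracking when the motor tests are repeated, while section 2.5.2 plans a pre-post gaze comparison. A larger false-alarm rate that counts EEG and gaze variables is therefore not supported.
- *That baseline mental fatigue goes unmeasured.* The FAS includes mental components, and the pre-task VAS covers momentary mental fatigue. The fault is one of labelling.

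**Conclusion.** The point holds in a limited form. The between-arm t-test at the pre time point cannot serve the aim it is placed under, and the post-time-point t-test leaves out a baseline value that the design relies on collecting. For outcomes other than EEG, section 2.6 states no between-arm analysis that uses the pre value.

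In roughly one randomisation in seven, a given variable will be out of balance by more than 0.5 SD, and most of those imbalances will not reach significance. In such a trial the post comparison would be off by 0.25 to 0.35 SD. This rests on 17 per arm, two-sided 5% tests and an assumed pre-post correlation of 0.5 to 0.7. The shift is conditional on the imbalance and is not a bias of the design as a whole. The 22% to 30% chance of a spurious baseline difference rests on a count of 7 variables and on the assumed correlation between them. The FAS label is a minor wording fault.

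**What to change.** 1. In section 2.6, replace the between-arm t-tests at each time point for VAS, LSPT, Y-SART and, where recorded at baseline, gaze outcomes. Use an ANCOVA of the post value on group and the outcome's own pre value, fixed in advance whatever imbalance is observed.
2. Reconcile this with the time-by-group ANOVA in the Discussion, stating which model applies to which outcomes.
3. Tabulate baseline values by arm as mean and SD, without p-values.
4. In section 2.5.4.1, call the FAS a measure of baseline general fatigue and use the pre-task VAS to describe baseline mental fatigue.

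The first item is a small change of analysis model and costs one degree of freedom per outcome. The rest is wording. No new data are needed and the planned sample size does not have to change.

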##### VAS

2.5.4.2

The VAS for mental fatigue, applied immediately before and after the cognitive induction task (ST), captures acute fluctuations in the subjective perception of fatigue. This 100 mm continuous scale, anchored between “no fatigue” and “extreme fatigue”, is sensitive to short-term changes induced by cognitive load and task duration (84). Within the experimental group, VAS ratings will be compared pre and post ST to quantify the immediate impact of the intervention on mental fatigue.

In addition, associations between subjective fatigue and other objective markers will be explored. Specifically, post-intervention VAS results will be correlated with EEG spectral characteristics (particularly alpha and theta power), oculomotor parameters (blink rate, pupil diameter, saccadic dynamics, and fixations), and motor performance measures (LSPT and Y-SART). This approach allows us to determine whether higher levels of self-reported fatigue align with neurophysiological and behavioral indicators of reduced performance, providing a multimodal framework for validating the perceptual dimension of fatigue.

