### Performance assessment

2.4

After collecting baseline data, participants will perform two motor tests as part of Phase 3 of the protocol. The first is the LSPT, which assesses passing accuracy and speed under time pressure in a standardized soccer-specific context. Participants perform 16 passes to designated targets announced in sequence, with performance assessed by total execution time adjusted for penalty points for technical errors (e.g., incorrect passes, errors in the target area, poor ball handling) and bonus points for accurate actions. This scoring protocol has been validated in youth and elite football players (56, 57). The test will be filmed with two cameras for subsequent technical analysis and penalty verification. A schematic representation of the LSPT setup is provided in Figure 2, adapted from Ali et al. (34).

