**Figure 3 F3:**
[figure not shown]
Schematic representation of the Y-SART, adapted from Yuan et al. (2).

After completing Phase 3, participants move on to Phase 4, where they perform the cognitive intervention defined by their group assignment, either the ST (experimental group) or a neutral task, such as reading magazines (control group). This is followed by Phase 5, which begins with participants completing the VAS again. Next, both motor tests are repeated, this time with continuous recording by the ETS. Finally, a second EEG recording is performed under the same conditions as in the initial phase, concluding the data collection session.

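### The schedule puts the first VAS before the motor tests, not directly before the induction task, so the experimental-group pre/post change cannot be read as the immediate impact of the Stroop task

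*Protocol article*

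**What the plan says.** The protocol article gives the timing of the first VAS in two ways.

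- Section 2.5.4.2 (VAS) says that it is "applied immediately before and after the cognitive induction task (ST").
- Section 2.3 (Mental fatigue assessment) refers to "the FAS and the VAS, which will be administered digitally during Phase 2". It says elsewhere only that the VAS comes before and after the cognitive task.

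Section 2.4 (Performance assessment) gives the order of what follows:

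- "After collecting baseline data, participants will perform two motor tests as part of Phase 3 of the protocol". These are the LSPT and the Y-SART.
- "After completing Phase 3, participants move on to Phase 4, where they perform the cognitive intervention defined by their group assignment".
- "This is followed by Phase 5, which begins with participants completing the VAS again". The repeat motor tests come after that rating.

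On content, section 2.3 says that the item "asks participants to indicate the intensity of fatigue felt at the moment", with anchors running from no fatigue to extreme fatigue. Section 2.5.4 introduces the FAS and VAS together as measures of mental and physical fatigue, while section 2.5.4.2 calls the scale a VAS for mental fatigue.

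On analysis, section 2.5.4.2 names one test of change: "Within the experimental group, VAS ratings will be compared pre and post ST to quantify the immediate impact of the intervention" on mental fatigue. Section 2.6 (Statistical analysis) is broader. It counts subjective fatigue ratings among the outcome variables, and plans paired t-tests in each group and independent t-tests between the groups at each time point.

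**The concern.** If the first rating is taken in Phase 2, a timed 16-pass football test and an agility test lie between it and the induction task. A rating of momentary fatigue may rise after such exertion. The experimental-group change would then mix three things: the Stroop task, what is left of the Phase 3 exertion, and the passage of time in the session. Section 2.5.4.2 attributes all of it to the intervention.

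This matters because the FAS is given once, at the start, so the VAS is the only repeated subjective measure of whether fatigue was induced. Section 2.5.6 and the Discussion also foresee reading preserved performance together with raised perceived fatigue as short-term compensation. If part of the rise comes from the motor tests, that reading loses support wherever it rests on the within-group change.

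**Working it through.** **Order of events, rebuilt from the text** (Figure 1 is not available here):

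| Phase | Content | Source |
|---|---|---|
| 2 | FAS, first VAS, first EEG | Section 2.3 |
| 3 | LSPT, then Y-SART | Section 2.4 |
| 4 | Stroop task or reading, 30 min | Sections 2.2 and 2.4 |
| 5 | Second VAS, then repeat motor tests, then second EEG | Section 2.4 |

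No rating is listed between Phases 3 and 4. In this order the first VAS is not immediately before the induction task, so section 2.5.4.2 and the schedule cannot both be right.

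**What each comparison contains.** Let M be the residual effect of Phase 3 and elapsed time on the second VAS, taken as equal in both arms. Let S and R be the effects of the Stroop and reading tasks.

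- Expected change, experimental group: M + S.
- Expected change, control group: M + R.
- Difference between groups: (M + S) − (M + R) = S − R.

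The within-group change cannot separate M from S. The between-group contrast is free of M. Both arms do the same Phase 3 tests before their tasks diverge, which makes a common M a reasonable starting point.

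**How far M alone could drive the experimental-group test.** The document states no figure on this point, so there is none to reproduce. The inputs are:

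- n = 17 per group, from section 2.2 (Sample);
- two-sided 5% level, from section 2.6;
- the residual rise d, in SDs of a single VAS rating, and the pre/post correlation ρ. Both are assumptions, because the document gives neither. Equal SDs at the two times are also assumed.

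The SD of the change is √(2(1 − ρ)) times the SD of one rating. The standardised change is therefore d_z = d / √(2(1 − ρ)), and the noncentrality of the paired t-test on 16 degrees of freedom is d_z × √17. The critical value is 2.12. With S = 0:

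| Assumed residual rise d | d_z at ρ = 0.5 | Significant | d_z at ρ = 0.8 | Significant |
|---|---|---|---|---|
| 0.1 SD | 0.10 | 7% | 0.16 | 9% |
| 0.2 SD | 0.20 | 12% | 0.32 | 23% |
| 0.3 SD | 0.30 | 21% | 0.47 | 45% |
| 0.5 SD | 0.50 | 49% | 0.79 | 86% |

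Example for the last row at ρ = 0.8: 0.5 / √0.4 = 0.79, and 0.79 × √17 = 3.26, which gives 86%. With no residual rise the rate is the nominal 5%.

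**The case against.** The strongest reply is that the plan does not rely on the experimental-group test alone. A reader of section 2.5.4.2 might infer that the VAS is tested only in that group, and so that the trial has no sound check on induction. The document does not support that inference. Section 2.6 covers subjective ratings with paired tests in both groups and between-group tests at each time point. The Introduction states the subjective-fatigue hypothesis against the low-load control. Section 2.5.6 plans group-level comparisons across the modalities, and the Discussion names an ANOVA for time and group interaction. A shared motor-test rise would also appear in the control group's own paired test. This part of the reply stands, and it limits the point to the within-group reading.

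Three further replies stand in part.

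- **Timing.** The Phase 2 sentence in section 2.3 is not a full VAS schedule, since it also leaves out the Phase 5 rating. Figure 1 might show a rating before Phase 4. The text nevertheless lists none, and describing the Phase 5 rating as a repeat fits the Phase 2 reading. What can be said firmly is that the sections conflict.
- **Size.** The shift would have to last through 30 minutes of Stroop or reading, and the document gives no basis for any particular residual. That is why a range is shown, and why its upper end should not be taken as an expected value.
- **Item wording.** One might infer that the item omits the word mental. The article paraphrases the item and describes it differently in different places, so this is something to confirm and not an established defect.

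**Conclusion.** The point holds in a limited form. The stated timing in section 2.5.4.2 contradicts the phase order in sections 2.3 and 2.4. As scheduled, the experimental-group change cannot measure the immediate impact of the Stroop task, because it includes whatever remains of the Phase 3 exertion and of elapsed time.

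The possible size ranges from slight (7% against a nominal 5%, at 0.1 SD and correlation 0.5) to severe (86%, at 0.5 SD and correlation 0.8). The rates rest on assumed shifts and correlations and describe only one of several planned VAS tests. They say nothing against the randomised between-group contrast, which stays valid and is unaffected if the motor-test effect is common to both arms. The correction is worth making before data collection, because a missing rating cannot be recovered afterwards.

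**What to change.** 1. Reconcile sections 2.3, 2.4 and 2.5.4.2, and Figure 1 if needed, on when the first VAS is taken.
2. Take the pre-induction VAS after the Phase 3 motor tests and directly before Phase 4, in both groups. The Phase 2 rating can be kept as a descriptive arrival value.
3. Confirm that the item asks about mental fatigue, and describe it in the same way in sections 2.3, 2.5.4 and 2.5.4.2.
4. In section 2.5.4.2, name the between-group difference in post-task VAS, adjusted for the pre-induction VAS, as the manipulation check. This matches the hypothesis in the Introduction. Report the experimental-group pre/post change as descriptive, and drop its description as the immediate impact of the intervention.

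The cost is one extra single-item rating, under a minute per participant, and a few sentences of text. The sample size does not change.
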